### Phase 1 research design and methods (1 year)

The goal of Phase 1 is to refine a fully functional prototype of LyssnCBT designed for CMH use and workflows. It will be integrated within the Lyssn cloud-based, software platform and make use of previously developed AI models for CBT fidelity. The prototype will be evaluated for usability and implementation readiness, and the Phase 1 milestones will establish readiness for a randomized evaluation of LyssnCBT in Phase 2.

#### Aim 1: Community Mental Health (CMH) user-centered design and software development

The LyssnCBT user-interface (UI) for CMH settings and workflows will be refined using an iterative, user-centered design (UCD) process so that the front-end UI of the system is maximally useful (and implementable) to a variety of end-users. Three groups of stakeholder participants will be recruited from sites previously trained in CBT by the BCI: therapists (*n* = 3), supervisors (*n* = 3) and clinic administrators (*n* = 4). Participants will be compensated $50 for their participation. The focus group and individual interviews will probe: typical client population, clinical and supervision workflows, current information technology (IT) infrastructure, and (administrators only) how quality assurance is currently conducted. A brief demonstration of the Lyssn platform and the existing CBT fidelity prototype will be provided. Participants will be queried about whether and how CTRS-based feedback is currently used within ongoing supervision, additional features of sessions and/or clients that would be useful for the LyssnCBT system to capture and report back, and perceived motivators and barriers to adoption of the LyssnCBT system.

Based on the input from the UCD design sessions, the research team will refine the design of the LyssnCBT software. It will build from Lyssn’s HIPAA-compliant cloud system, and while final features and functions will be shaped by the design sessions, the LyssnCBT UI is anticipated to include interactive summaries of CBT fidelity scores (individual items, plus total), allowing summarization of ranges of sessions, clients, and therapists along with drill down to individual sessions for review and supervision.

#### Aim 2: usability and implementation readiness of LyssnCBT with standardized patients

After the LyssnCBT software is adjusted to reflect the UCD feedback, usability and implementation readiness will be assessed using standardized patient (SP) methodology. Ten CMH therapists and five supervisors will be recruited to participate in an individual, 60–90 min session, including an SP “therapy” session and semi-structured interview. (Note: Supervisors will not record SP sessions and interview questions will be framed around supervision processes, but otherwise will be largely similar to therapist sessions.) There will be a brief introduction to the Lyssn recording platform, and then each therapist will use it to record a 15-min session with the SP (played by a study team member), treating it as if it were a regular therapy session at their clinic. The recorded therapy session will be processed by LyssnCBT. The therapist participants will then be guided through the LyssnCBT interface, which will display the SP session just recorded along with other roleplayed sessions pre-recorded by the research team. During the semi-structured interview, participants will be solicited for feedback on UI elements, including visualizations of CBT measures, data fields, and navigation controls. Participants will then be asked how they would imagine using LyssnCBT to complete critical actions, like assessing their performance during a clinical session or reviewing a session during supervision. At the end of the sessions, therapist and supervisor participants will complete brief (4-item) implementation measures of acceptability (Acceptability of Intervention Measure; AIM; [61]), appropriateness (Intervention Appropriateness Measure; IAM; [61]), and feasibility (Feasibility of Intervention Measure; FIM; [61]), as well as usability (System Usability Scale; SUS; [62]) with respect to the LyssnCBT prototype. The research team will review and refine the LyssnCBT platform based on the feedback gathered in this stage.

### Phase 2 research design and methods (3 years)

The primary research activity of Phase 2 is a type 2 hybrid implementation-effectiveness, randomized study comparing LyssnCBT for clinical and supervision services to services as usual (SAU), where the primary outcomes include therapist CBT skill and client outcomes (symptom improvement and drop-out). Working closely with DBHIDS leadership, 5 programs will be recruited from among the Penn Collaborative / BCI CMH partner organizations, targeting adult outpatient mental health clinics with 8 or more staff therapists. Agency participation will include the integration of LyssnCBT on a program level to facilitate the integration of LyssnCBT into standard workflow practices including requesting consent to record and participate from clients during the standard intake process, and integration into supervision practices. Therapists (*n* = 50) and their supervisors will be recruited, where each therapist will have a caseload of about 5 clients participating in the study at any given time. (Note: Participating therapists may use LyssnCBT with as many of their clients as they wish, but they will be asked for a minimum of 5 clients consenting to participate in study data collection at any given time.) Median treatment length at DBHIDS clinics is approximately 10 weekly sessions. Across 18 months of planned data collection (~ 75 weeks), recruitment is expected to yield a minimum of 1,875 clients (i.e., 50 therapists × 5 sessions per week × 75 weeks = 18,750 sessions, with an average of 10 sessions per client).

LyssnCBT will be compared to SAU using a stepped-wedge design in which each clinic will have SAU and LyssnCBT phases. Stepped wedge designs allow the intervention (here, LyssnCBT) to eventually roll out to all clinics and therapists and also has greater power than a parallel cluster randomized trial [63]. As shown in Fig. 2, all 5 clinics will start with SAU (black solid lines), and clinics will be randomized to begin LyssnCBT sequentially over time (dashed purple) using simple randomization. The names of the five participating agencies will each be enclosed in individual sealed envelopes, and every two months, a study team member will select one envelope with the name of the agency to begin LyssnCBT. At the start of the trial when all clinics are in the SAU phase, all clinics will begin using a modified version of the Lyssn platform for recording sessions that provides access to the recording and session sharing functionality, but no other features (e.g., speech-to-text transcription, annotation tools, any AI-generated metrics). When a clinic is randomly selected to use LyssnCBT, there will be an onboarding and training session to cover the software and clinical / supervision protocols. Participants may withdraw or take away permission to use and disclose their information at any time by sending written notice to the investigator for the study. If they withdraw their permission, they will not be able to stay in the study.

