### Participants and procedures

For Phase 1, Project AFFECT will recruit therapists, supervisors, and administrators (*n* = 25) from within the DBHIDS network. Inclusion criteria will include being currently employed at an adult outpatient CMH program that has received CBT training and implementation support from the BCI and being able to engage in study processes in English. For Phase 2, the Project AFFECT study team will identify 5 adult outpatient CMH programs from among the BCI partner programs who agree to integrate LyssnCBT into their routine procedures. Across the 5 agencies, therapists (*n* = 50) and their supervisors will be recruited for participation. Clients from the caseloads of participating therapists will be recruited to participate, with a goal of 5 consenting clients per therapist. Median treatment length at DBHIDS programs is approximately 10 weekly sessions. Across 18 months of planned data collection (~ 75 weeks), a minimum of 1,875 clients for 50 therapists are expected (i.e., 50 therapists × 5 sessions per week × 75 weeks = 18,750 sessions, with an average of 10 sessions per client).

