#### Assessments / outcomes

There are two classes of primary outcomes: a) therapist CBT fidelity, and b) client outcomes. CBT fidelity will be assessed by AI-generated CTRS scores for every recorded therapy session, which will be recorded via the Lyssn platform during both SAU and LyssnCBT phases of the study (approximately 18,750 sessions in total). Client outcomes will be evaluated using the Patient Health Questionnaire-9 (PHQ-9) and Generalized Anxiety Disorder-7 (GAD-7) at each session. The PHQ-9 is a brief, widely used depression inventory with 9 total items, and similarly, the GAD-7 is a brief, widely used anxiety inventory with 7 total items [64–66]. The PHQ-9 and GAD-7 are reliable and valid and can be completed in 2–3 min. These client self-report measures will be collected via a web-based survey tool that supports text and email notification via URL to complete assessments and integrates with the Lyssn platform. Before a participating therapist begins a new session using the Lyssn platform, an email (or text) notification will be sent to the client to complete the PHQ-9 and GAD-7. Data will also be collected on client drop-out / premature termination via a brief monthly survey sent out to participating therapists. Finally, after three months of engagement with the LyssnCBT tools, each participating therapist and supervisor will complete the battery of implementation measures, including the SUS, AIM, IAM, and FIM, as well as have an opportunity to provide more general feedback on the LyssnCBT system. All assessments are summarized in Table 1. Therapists and supervisors will receive a gift card worth $30 for attending a Lyssn onboarding session and $20 for completing implementation measures. In addition, therapists will be compensated $15 per participating client. Clients will be compensated with one $10 gift card for allowing the research team access to the data from their weekly symptom measures and session recordings.

**Table 1 Tab1:** Summary of Phase 2 data collection

Participant	Construct	Measures	Frequency and timeline
*Client*	Depression, Anxiety	PHQ-9, GAD-7	Before each session
	Drop-out from treatment	Survey	Once a month
*Therapist*	CBT fidelity	CTRS	After each session
	Implementation outcomes	AIM, IAM, FIM, SUS	Once, 3 months after start of LyssnCBT phase
*Supervisor*	Implementation outcomes	AIM, IAM, FIM, SUS	Once, 3 months after start of LyssnCBT phase

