### Potential for impact

The DBHIDS network includes over 300 agencies. Conservatively assuming that each agency has 10 therapists and each therapist sees 30 clients per week, that is 90,000 sessions per week, approximately 4.5 million per year – in *one* publicly-funded behavioral health system in a single large American city. There are currently no feasible methods for estimating the quality of even a fraction of those sessions. The current research builds upon a robust, existing platform and lays the groundwork for a feasible, technology-enabled assessment of CBT intervention quality at scale, which can inform performance-based feedback for training, supervision, and quality assurance. The combination of the team, the project, and the partnership with DBHIDS presents a unique opportunity to massively scale up quality monitoring of CBT interventions, and the underlying methodologies would lay a foundation for psychosocial intervention quality monitoring and feedback in general. The implications of this research would be improved outcomes for clients, improved support for therapists, and improved quality assurance processes for behavioral healthcare systems.

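### Clients enrol while staff know the clinic's phase, and the stated model does not adjust for entry severity, so a change in who enrols would be read as a LyssnCBT effect

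*Protocol article*

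**What the plan says.** The section on Phase 2 research design and methods describes a stepped wedge in five clinics. All start in SAU, and "every two months, a study team member will select one envelope with the name of the agency to begin LyssnCBT". The drawn clinic then receives onboarding and training, so its staff know the current phase.

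Three statements bear on how clients enter:

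- Agencies build the study into their routine workflow, including "requesting consent to record and participate from clients during the standard intake process" (Phase 2 research design and methods).
- "Clients from the caseloads of participating therapists will be recruited to participate, with a goal of 5 consenting clients per therapist" (Participants and procedures).
- Of therapists: "they will be asked for a minimum of 5 clients consenting to participate in study data collection at any given time" (Phase 2 research design and methods).

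The PHQ-9 and GAD-7 are completed before each session (Assessments / outcomes, Table 1). The Data analysis plan specifies mixed models with condition, separate time slopes by phase and clinic dummies. Its primary focus is the main effect of condition and its interaction with time. It names no client-level covariate. The sensitivity analyses it describes concern missing recordings and questionnaires.

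**The concern.** In a stepped wedge, randomisation fixes the order in which clinics switch. It does not fix which clients enter before or after the switch. When clients are enrolled after the phase is known, the two phases can contain different kinds of client even though the clinic order was random.

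The article names an intake route and a caseload route, and gives a floor of five. It does not say how these combine, or that the approach to clients stays the same after a clinic switches. If clients enrolled under LyssnCBT were less severe at entry than those enrolled under SAU, the difference would enter the condition main effect on PHQ-9 and GAD-7, and could carry over to drop-out. Clinic dummies remove stable differences between clinics. They do not remove a change within a clinic at its switch. A larger sample would not help either, because this is bias and not imprecision.

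**Working it through.** **1. The plan's own client count.** Inputs from Phase 2 research design and methods: 50 therapists, 5 sessions per week, 75 weeks, 10 sessions per client.

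50 × 5 × 75 = 18,750 sessions; 18,750 / 10 = 1,875 clients. The stated figure is reproduced.

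**2. How many clients are seen in both phases.** Each clinic switches once. With about 5 study clients per therapist in treatment at that moment:

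50 × 5 = 250 clients; 250 / 1,875 = 13.3%. The other 86.7% contribute to one phase only. The condition contrast on client outcomes is therefore mainly between different clients.

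**3. What the stated model absorbs.**

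- Clinic dummies absorb stable differences between clinics.
- Time by phase absorbs trends within each phase.
- No stated term absorbs a step in client severity that coincides with the switch. Such a step has the same form as the condition main effect.

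**4. Illustration of size.** The target from Power and sample size is d = 0.15. The article gives no PHQ-9 SD, so I assume 5 to 6 points.

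| Assumed SD | Target in points | 0.5-point entry difference in SD | Share of target |
|---|---|---|---|
| 5 | 0.15 × 5 = 0.75 | 0.5 / 5 = 0.100 | 0.5 / 0.75 = 67% |
| 6 | 0.15 × 6 = 0.90 | 0.5 / 6 = 0.083 | 0.5 / 0.90 = 56% |

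The 0.5 point is a chosen example, not an estimate.

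**5. What a shift would do to the test.** I take the stated power of 0.80 at d = 0.15 as given and assume a two-sided 5% test. The implied standard error is 0.15 / (1.960 + 0.842) = 0.0535. With no true effect and a shift b that passes fully into the condition term, the probability of a significant result is 1 − Φ(1.960 − b/0.0535) + Φ(−1.960 − b/0.0535):

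- b = 0.05 SD: 15%
- b = 0.10 SD: 46%
- b = 0.15 SD: 80%

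**The case against.** The strongest reply is that intake consent at programme level is already close to the remedy. If every intake were asked in the same way in both phases, staff would have little room to influence who enters. Clients who have been taken in and assigned also make up a caseload, so the two descriptions can be compatible. A condensed article commonly leaves approach order and screening logs to the full protocol. Rolling enrolment in open clinics is common in stepped-wedge trials. The first-session score is collected, so adjustment remains possible.

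Much of this stands, and it rules out several stronger readings:

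- *Therapists hand-pick any five clients.* No text says so. "Participating therapists may use LyssnCBT with as many of their clients as they wish" concerns use of the software, and the floor of five for data collection is stated separately from it.
- *Payment drives the selection.* "therapists will be compensated $15 per participating client" is not tied to phase. It may encourage enrolment, but it gives no reason for a difference between phases.
- *Recordings have no consequence in SAU, while every LyssnCBT session is reviewed with the supervisor.* Neither is stated. SAU clinics can share sessions, and the Data management section says that feedback reports are viewed together in supervision, not that every session is.
- *Five is a small fraction of the caseload.* Potential for impact reads "Conservatively assuming that each agency has 10 therapists and each therapist sees 30 clients per week", which would make five 5/30 = 17%. That is a network-wide illustration, not data from the study clinics, and it says nothing about who selects.
- *Nobody is blind.* What clients are told about phase is not described. Staff of a clinic still in SAU know its current phase but not its future switch date.

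What the objection does not remove is the model. The article sets out its terms, and none of them covers client severity at entry. Even with every intake invited, willingness to consent could differ between phases.

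**Conclusion.** The point holds as a risk that the stated analysis leaves open. Clients enter after the clinic's phase is known to staff, about 87% are seen in one phase only, and the described model would attribute any phase-related difference in entry severity to LyssnCBT. The document does not show that such selection will happen, and its size is unknown.

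The 87% assumes a steady five study clients per therapist at each switch. The 56% to 67% rests on an assumed SD and an assumed 0.5-point difference. The false-positive rates rest on the stated power, a two-sided 5% test and a shift that passes fully into the condition term. The point does not show that the sample size is wrong. The change is worth making because the trial is sized for a small effect and the adjustment uses data already collected.

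**What to change.** 1. **Model.** Add the client's PHQ-9 or GAD-7 score before the first study session as a covariate in the corresponding symptom model, with later sessions as the outcome. Include these scores in the drop-out model as well.
2. **Enrolment.** State that, in both phases, intake staff invite new clients of participating therapists consecutively whenever a study place is open. Say how this fits with recruitment from caseloads: for a client who joins in mid-treatment, the first study score is not a pre-treatment score.
3. **Reporting.** Count clients invited and consenting by clinic and phase, and report them with the entry scores.

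The covariate addresses measured severity only. Differences in engagement or suitability for CBT, which could also affect CTRS scores, are addressed by the enrolment rule and made partly visible by the counts.

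Cost: protocol wording, a simple intake count at each clinic and slightly slower filling of places. The first score is lost as an outcome, about 1,875 of 18,750 planned measures (10%), which leaves 16,875. Clients with a single session would contribute to the drop-out model but not to the symptom models.

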**Fig. 2 Fig2:**
[figure not shown]
Phase 2 study design overview

#### Assessments / outcomes

There are two classes of primary outcomes: a) therapist CBT fidelity, and b) client outcomes. CBT fidelity will be assessed by AI-generated CTRS scores for every recorded therapy session, which will be recorded via the Lyssn platform during both SAU and LyssnCBT phases of the study (approximately 18,750 sessions in total). Client outcomes will be evaluated using the Patient Health Questionnaire-9 (PHQ-9) and Generalized Anxiety Disorder-7 (GAD-7) at each session. The PHQ-9 is a brief, widely used depression inventory with 9 total items, and similarly, the GAD-7 is a brief, widely used anxiety inventory with 7 total items [64–66]. The PHQ-9 and GAD-7 are reliable and valid and can be completed in 2–3 min. These client self-report measures will be collected via a web-based survey tool that supports text and email notification via URL to complete assessments and integrates with the Lyssn platform. Before a participating therapist begins a new session using the Lyssn platform, an email (or text) notification will be sent to the client to complete the PHQ-9 and GAD-7. Data will also be collected on client drop-out / premature termination via a brief monthly survey sent out to participating therapists. Finally, after three months of engagement with the LyssnCBT tools, each participating therapist and supervisor will complete the battery of implementation measures, including the SUS, AIM, IAM, and FIM, as well as have an opportunity to provide more general feedback on the LyssnCBT system. All assessments are summarized in Table 1. Therapists and supervisors will receive a gift card worth $30 for attending a Lyssn onboarding session and $20 for completing implementation measures. In addition, therapists will be compensated $15 per participating client. Clients will be compensated with one $10 gift card for allowing the research team access to the data from their weekly symptom measures and session recordings.

**Table 1 Tab1:** Summary of Phase 2 data collection

Participant	Construct	Measures	Frequency and timeline
*Client*	Depression, Anxiety	PHQ-9, GAD-7	Before each session
	Drop-out from treatment	Survey	Once a month
*Therapist*	CBT fidelity	CTRS	After each session
	Implementation outcomes	AIM, IAM, FIM, SUS	Once, 3 months after start of LyssnCBT phase
*Supervisor*	Implementation outcomes	AIM, IAM, FIM, SUS	Once, 3 months after start of LyssnCBT phase

*PHQ-9* Patient Health Questionnaire-9, *GAD-7* Generalized Anxiety Disorder-7, *CTRS* Cognitive Therapy Rating Scale, *AIM* Acceptability of Intervention Measure, *IAM* Intervention Appropriateness Measure, *FIM* Feasibility of Innovation Measure, *SUS* System Usability Scale

#### Data analysis plan

CBT fidelity, client symptom measures (PHQ-9, GAD-7), and client drop-out will be analyzed with mixed-effects models (also called hierarchical or multilevel models; [67–70]). Mixed models are very flexible with respect to nested and imbalanced data, where the current data will contain repeated measures within clients and within therapists with varying numbers of sessions and clients. Within each individual clinic, a stepped wedge design is similar to an interrupted time series, with pre-intervention (i.e., SAU) and post-intervention (i.e., LyssnCBT) phases. To model the intervention effect, separate slopes will be examined for time by phase to capture differential changes in outcomes across the two phases. *Condition* (LyssnCBT vs SAU) will be dummy-coded, and clinics will also be included in the model as dummy-coded control variables. Analyses across the outcomes will be very similar, with the exception that client drop-out is a binary outcome, whereas a logistic mixed effects model will be used instead. The primary focus in all analyses is the main effect of *Condition* and its interaction with *Time* (during the phase since LyssnCBT started). Finally, sensitivity analyses will examine missing data. Missing data could be a function of a therapist not recording a session, or of a client not completing self-report measures. The research team will review weekly reports of anticipated recordings and assessments to prevent missing data whenever possible. No significant challenges with missing data are anticipated, though calculations have assumed 20% attrition in power analyses (see below). Mixed-effects models provide unbiased estimates in the presence of missing data as long as missing data can be assumed Missing at Random (MAR; [70]). If missing data is greater than 20% or there are other concerns about the MAR assumption, a pattern-mixture approach will be used to (potentially) non-ignorable missing data [71].

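### The pattern-mixture analysis for PHQ-9 and GAD-7 depends on a 20% missing-data trigger or undefined MAR concerns; the percentage does not test MAR and can hide a difference between phases

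*Protocol article*

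**What the plan says.** All statements are in the Protocol article.

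- **Main analysis and its assumption** (Data analysis plan): "Mixed-effects models provide unbiased estimates in the presence of missing data as long as missing data can be assumed Missing at Random".
- **Trigger for the alternative** (same section): "If missing data is greater than 20% or there are other concerns about the MAR assumption", in which case "a pattern-mixture approach will be used to (potentially) non-ignorable missing data". The section does not say what would count as a concern, what the 20% is a share of (sessions, clients or forms), or whether it is taken overall or by phase.
- **General statement** (same section): "Finally, sensitivity analyses will examine missing data". Pattern-mixture is the only non-ignorable method named.
- **Sources of missing data** (same section): "Missing data could be a function of a therapist not recording a session, or of a client not completing self-report measures". Drop-out is not on this list.
- **Power allowance** (same section): "calculations have assumed 20% attrition in power analyses".
- **Timing of the scales** (Assessments / outcomes, Table 1): PHQ-9 and GAD-7 are requested before each session. No assessment after a client leaves treatment is described.
- **Drop-out**: it is a primary client outcome alongside symptom improvement (Phase 2 research design and methods), LyssnCBT is meant to reduce it (Abstract, Methods), and it has its own logistic mixed model (Data analysis plan).

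**The concern.** MAR is a statement about why scores are missing: given what was observed, missingness must not depend on the values that were not seen. The share of scores missing says nothing about that. A small loss can breach MAR and a large one can satisfy it. The first arm of the trigger therefore measures the wrong quantity. Its cut-off also coincides with the power allowance, so a trial that loses exactly what was allowed for does not meet it.

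In this trial symptom scores are tied to sessions, so they end when a client leaves, and the intervention is intended to change how many leave. If the intervention works as hoped, loss of scores will differ between phases, and an overall percentage averages that difference away. Drop-out is also missing from the listed sources of missing data. A client who has left has no session to record and no form falling due, so scores lost this way might not enter the 20% count at all.

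At stake is the PHQ-9 and GAD-7 comparison. It could be reported on MAR alone, with the decision to look further taken after the data are seen and on no stated criterion.

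**Working it through.** **1. The plan's own figures.** 50 × 5 × 75 = 18,750 sessions, and 18,750 / 10 = 1,875 clients; both reproduce. The target effect is d = 0.15 (Power and sample size). The 20% appears in the Data analysis plan as a power allowance, not as a forecast.

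**2. How the phases weigh in an overall percentage.** One clinic switches every two months over 18 months of data collection. Assuming the first switch is at month 2, clinic-months under SAU are 2 + 4 + 6 + 8 + 10 = 30 of 5 × 18 = 90, or 1/3. With sessions spread evenly, overall share = p_SAU/3 + 2·p_Lyssn/3.

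| Missing, SAU | Missing, LyssnCBT | Overall | Above 20%? |
|---|---|---|---|
| 20% | 10% | 0.0667 + 0.0667 = 13.3% | no |
| 40% | 10% | 0.1333 + 0.0667 = 20.0% | no, exactly at it |

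A fourfold difference between phases can leave the percentage arm unmet.

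**3. Bias from a non-ignorable shift.** Higher scores are worse. Suppose unseen scores in a phase lie δ SD above what the MAR model predicts. The true phase mean is then the MAR mean plus p·δ. The LyssnCBT-minus-SAU contrast is therefore biased by p_SAU·δ_SAU − p_Lyssn·δ_Lyssn, which with a common δ is (p_SAU − p_Lyssn)·δ. The missing shares and δ are assumptions; no document gives them.

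| δ (SD) | (0.20 − 0.10) × δ | Share of 0.15 |
|---|---|---|
| 0.3 | 0.03 | 20% |
| 0.5 | 0.05 | 33% |
| 0.8 | 0.08 | 53% |

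*Direction.* The sign is positive: SAU looks too good and a LyssnCBT benefit is understated. If more is missing under LyssnCBT, or if unseen scores are better than predicted, the sign reverses and the benefit is overstated. Equal missingness with equal δ gives zero. Equal missingness with unequal δ does not, which is why the shift should be allowed to differ by phase.

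**4. Simulation of the mixed model.** Assumed set-up: 10-session courses; no true phase effect; equal numbers in the two phases; random-intercept SD 0.8, random-slope SD 0.06 and residual SD 0.45; generalised least squares with known variances. One unit is about one SD of the score: √(0.64 + 0.2025) = 0.92 at the first session and √(0.64 + 0.2916 + 0.2025) = 1.06 at the last. The table gives the estimated final-session difference, which should be 0.

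| Leaving depends on | Drop-out, SAU / LyssnCBT | Sessions missing overall | Estimate |
|---|---|---|---|
| last observed score (MAR) | 37% / 20% | 15.8% | 0.001 |
| last observed score (MAR) | 45% / 16% | 17.0% | −0.001 |
| current unseen score | 37% / 20% | 15.8% | 0.028 |
| current unseen score | 45% / 16% | 17.0% | 0.051 |
| client's own slope | 36% / 20% | 15.4% | 0.057 |
| client's own slope | 43% / 15% | 16.5% | 0.101 |

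Monte Carlo standard errors are 0.002 to 0.003. With equal drop-out in the two phases (28 to 29% each) every mechanism gave an estimate within 0.002 of zero. All rows lie below 20% missing. What separates a biased row from an unbiased one is the mechanism together with the phase difference; the overall percentage is nearly the same throughout.

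**The case against.** The case for leaving the text as it is has five parts.

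- **The trigger has two arms.** A marked imbalance between phases would be an obvious concern about MAR, so pattern-mixture could still be run. A reader might infer that the plan rules it out below 20%; it does not. What stands is that the second arm has no criterion and would be applied with the data in view.
- **Drop-out would not be hidden.** It is modelled by Condition as a primary outcome, and recordings and assessments are reviewed weekly. This stands for drop-out itself. It does not show how the symptom estimate responds to scores that were never seen.
- **Unequal drop-out is not a breach of MAR.** A reader might infer that session-linked scores make MAR fail by design. The documents do not support that: phase is in the model, clients contribute scores at every session, and the simulated MAR cases gave no bias even at 45% against 16%. Bias needs dependence on unseen values, which nothing in the documents shows and which the observed data cannot rule out.
- **The 20% is a power allowance.** A reader might take it as the expected level of missing data. The plan says it anticipates no significant challenges, and attrition need not be the same quantity as missing sessions or forms. Only the coincidence of the two figures stands.
- **This is detail for the analysis plan.** Definitions and tables can be left there. The trigger is different: the article itself fixes it.

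**Conclusion.** The point holds as a weakness in a stated rule, not as a demonstrated bias. The percentage arm cannot tell whether MAR is tenable, and it can remain unmet while phase-dependent, non-ignorable loss moves the symptom estimate. The other arm is undefined.

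Under the assumed shares and gaps the shift is 0.03 to 0.08 SD against a target of 0.15; the simulation gives 0.03 to 0.10 SD, about one fifth to two thirds of the target. These sizes rest on the assumed missing shares, shifts and variance components, on a fixed course length although real courses vary, and on a phase-mean or final-session contrast. The effect on the Condition-by-Time term was not derived. In these examples the error is conservative for LyssnCBT, but the direction is not guaranteed. That PHQ-9 and GAD-7 stop at drop-out is inferred from their session-linked collection. The main model can stay as it is.

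**What to change.** In the Data analysis plan:

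1. Remove the trigger, so that the pattern-mixture sensitivity analysis is run for PHQ-9 and GAD-7 whatever the percentage missing.
2. Use a separate shift for unobserved scores in each phase, and report the shift at which the Condition conclusion changes.
3. Name drop-out as a source of missing symptom scores.
4. Report missingness by phase, stating what is counted.

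The cost is a brief change of text and one extra analysis of data already held. The downside is one more sensitivity result to report and interpret. The main model and data collection do not change.
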